##### Azathioprine

TPMT genotype or phenotype at screening determines the initial dose of AZA/6MP; and measurement of thiopurine metabolites (6-TG and 6-MMP) at visit 2 determines requirement for subsequent dose adjustment performed according to the recommendations in table 3. Where possible thiopurine metabolites are measured locally; central lab measurements are provided for centres where this is unavailable.

At visit 2, a urine sample for TPMT metabolite determination and an erythrocyte lysate sample for quantification of thiopurine nucleotides by liquid chromatography-tandem mass spectrometry should be frozen at −80°C and shipped on dried ice to the central lab at the end of the study. At each visit from visit 2–6, an additional ethylenediaminetetraacetic acid (EDTA) blood sample will be collected for further 6-TG and 6-MMP testing and frozen at −80°C.

##### Methotrexate

Washed erythrocyte for MTX levels will be obtained at visits 2, 4 and 6 and stored frozen at local centres. These samples will be sent on dry ice for central analysis to evaluate response to therapy and adverse effects in relation to drug levels.

##### Adalimumab

ADA trough levels are measured after three injections of maintenance therapy (eg, at visit 2) within the local laboratory (central lab testing available if local lab testing is unavailable). Dosing interval may be shortened to weekly in the event of low ADA levels (<8 μg/mL) and negative ADA antibodies. Further samples should be obtained at visits 3, 4, 5 and 6 and should be frozen for later analysis within the central lab.

##### Pharmacogenetics

DNA for pharmacogenetics should be taken from patients randomised to MTX or AZA/6MP for multiplex genotyping of polymorphism related to drug metabolism to evaluate safety and response to therapy. Analysis will be performed at the end of the study, or earlier in those patients showing toxicity.

#### Ancillary study

Patients unable to discontinue induction therapy or those randomised to thiopurine or MTX therapy who experience treatment failure may be invited to participate in the ancillary study (STEP-up ADA) until visit 5. Any initial maintenance therapy will be stopped and induction and maintenance regime for ADA as previously described will be commenced. Up to three additional study visits at 3-month intervals will be offered to these patients in order to obtain 12 months of follow-up. A maximum of 68 patients can participate in this ancillary study allowing a 1:1 comparison of top-down ADA to step-up ADA therapy.

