Box 1Study endpointsPrimary endpointSustained steroid/exclusive enteral nutrition (EEN)-free remission at month 12, where sustained remission is defined as weighted Paediatric Crohn’s Disease Activity Index (wPCDAI) ≤12.5 and C reactive protein (CRP) ≤1.5 times the upper limit without a relapse or need for EEN/steroids since week 12.Secondary endpointsComparing the following within (1) the two treatment arms per risk group; (2) methotrexate treatment between high and low-risk groups and (3) tOP-down adalimumab (high-risk group) versus step-pp adalimumab (ancillary study):Rate of clinical remission at month 12 (physician global assessment, wPCDAI, PCDAI).Relapse free remission with normal CRP at month 12.Relapse-free remission with normal CRP and faecal calprotectin <300 at month 12.Remission at week 12 (measured by wPCDAI≤12.5 and normal CRP and being off steroids/EEN).Time to first relapse after week 12.Predictive value of faecal calprotectin values at visits 1, 2, 4 and 6 (respectively at month 0, 2, 6 and 12).Drop-out rates.Adverse drug event rate including pharmacogenomics for toxicity and response to therapy.Height velocity and z-score at baseline and 52 weeks.Quality of life as measured by the IMPACT 3 questionnaire completed at each study visit.Health economic evaluation at all visits (forms EQ-5D-Y proxy 1, EQ-5D-Y and EQ-5D-5L, Productivity and Activity Impairment Questionnaire (WPAI):Crohn’s disease Caregiver, School Attendance start of the research and follow-up visits).

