### Secondary analyses

X^2^ tests or Fisher’s exact tests will be used to compare rates of remission, steroid intake, drop-out and SAEs between the two arms of each risk group and between the low and high-risk MTX groups. Logistic regression analyses may be performed to adjust for any imbalances in baseline covariates. To compare time to disease flare between the arms of each risk group and between high and low-risk MTX groups, a Kaplan-Meier survival estimate will be used and the log-rank test of equality over strata. A Cox proportional hazard model will be constructed to obtain a HR after validation of the proportionality assumption and adjusting for possible confounding variables (including age and disease duration). Student’s t tests or Wilcoxon rank sum tests will be used to compare growth, steroid dose, adverse events, changes in quality of life and patient reported outcomes between the two arms of each risk group and between the high and low-risk MTX groups. The predictive value of faecal calprotectin levels, CRP, serum tests or other clinical predictors for response (including genomic and serological markers) will be assessed for each arm of the study using sensitivity, specificity, negative and positive predictive values or area under the receiver operating characteristic curve. Multivariate logistic regression analyses will then be performed.

Analyses will be performed using the R software (http://cran.r-project.org). All comparisons will be made using a two-sided significance level of 0.05.

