#### Sample size considerations

Estimated remission rates are based on recent analysis from the RISK study,^18^ indicating an advantage of early anti-TNF introduction over immunomodulator therapy. For the low-risk group, it was hypothesised that 48% of children will be in remission at 12 months for the AZA/6MP arm versus 70% for the MTX arm. On the basis of this data with an alpha risk of 5% and a power of 80% a sample requirement of 88 patients per arm was calculated assuming a 10% lost to follow-up. For the high-risk group, it was hypothesised that 40% of children will be in remission at 12 months for the MTX arm versus 65% for the ADA arm. To detect this difference with an alpha risk of 5% and a power of 80%, a sample size of 68 participants is necessary, again assuming a 10% lost to follow-up. In total 312 participants will be included in the study (176 low-risk group; 136 high-risk group).

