In addition to this, the ancillary study will compare outcomes in ADA treated patients from inclusion (top-down) versus patients switched to ADA due to failure of immunomodulators (step-up), with the potential to stratify which patients might benefit from such a top-down treatment strategy. We acknowledge that comparison of the ancillary group with the group randomised from baseline to ADA is not randomised and may be subject to selection bias noting the ancillary group have failed or been intolerant to initial therapy. However, we feel it is important to include this to allow us to compare the trial with studies which have allocated patients directly to anti-TNF (RISK, TISKids) and to see how many patients benefit from ‘rescue therapy’ after failure of their initial allocation.

The design and completion of interventional studies in PIBD is a recognised challenge between rigorous study design methodology and pragmatic considerations around feasibility and completion within a paediatric dataset.^25^ This particular study is limited by the inability to blind the treatment allocation to the patients, their families or their treating physician due to the differences in medication administration route and the side effects commonly associated with the study medication. Although the protocol advises that where possible blinding of an alternative clinician to score disease assessment at each study visit should occur in order to obtain PROBE evaluation, this may be practically difficult in smaller centres where staff are familiar with the majority of their patient cohort.

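### The ancillary top-down versus step-up adalimumab comparison confounds strategy with risk group, and the article's caveat names only selection by prior failure

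*Protocol article*

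**What the plan says.** Under Study design, adalimumab is a randomised arm only for high-risk children. Low-risk children are randomised to methotrexate or a thiopurine.

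The Ancillary study section opens step-up adalimumab to children who cannot stop induction therapy and to those in whom a thiopurine or methotrexate has failed. It sets a cap but no restriction or quota by risk group: "A maximum of 68 patients can participate in this ancillary study allowing a 1:1 comparison of top-down ADA to step-up ADA therapy".

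Box 1 (Study end points) makes this one of three comparisons to be run across all the listed secondary endpoints: top-down "adalimumab (high-risk group) versus step-pp adalimumab (ancillary study" (misspelling in the article). The last paragraph of the Introduction poses the top-down question for high-risk children only.

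The Discussion accepts that the comparison is not randomised and "may be subject to selection bias noting the ancillary group have failed or been intolerant to initial therapy". It still sees potential in it for identifying the patients who would gain from top-down treatment. It does not mention the risk mix.

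**The concern.** Risk group separates the two sides of the comparison, and the plan itself treats it as strongly prognostic. On the same drug, methotrexate, Sample size considerations assumes 70% remission in low-risk and 40% in high-risk children, a gap of 30 points. One side of the comparison is entirely high-risk and the other is a mixture.

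A difference in either direction, or no difference, could then arise without any effect of strategy. What is at stake is the claim that the ancillary study can help show which children benefit from top-down treatment. The Introduction asks this for high-risk children, and the pooled step-up group does not represent them.

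**Working it through.** **Inputs** (Sample size considerations unless stated)
- Low-risk: "48% of children will be in remission at 12 months for the AZA/6MP arm versus 70% for the MTX arm"; 88 per arm.
- High-risk: "40% of children will be in remission at 12 months for the MTX arm versus 65% for the ADA arm"; 68 per arm.
- Loss to follow-up 10%; ancillary cap 68 (Ancillary study).
- "with an alpha risk of 5% and a power of 80% a sample requirement of 88 patients per arm was calculated"; sidedness from Secondary analyses: "All comparisons will be made using a two-sided significance level of 0.05".

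**Reproducing the plan's sample sizes.** Per arm, n = [1.96·√(2·p̄(1−p̄)) + 0.842·√(p1(1−p1) + p2(1−p2))]² / (p1−p2)², then divided by 0.9.
- High-risk, 0.40 v 0.65: 62, inflated to 69 (stated 68).
- Low-risk, 0.48 v 0.70: 78, inflated to 87 (stated 88).

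Both agree to within one patient, so the rates and arm sizes are safe to use.

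**Expected risk mix of the step-up group.** The article gives none. Taking month-12 non-remission as a stand-in for failure, expected failures are n × (1 − remission rate):
- AZA/6MP (low-risk): 88 × 0.52 = 45.8
- MTX, low-risk: 88 × 0.30 = 26.4
- MTX, high-risk: 68 × 0.60 = 40.8
- Total 113.0

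Low-risk share = (45.8 + 26.4)/113.0 = 63.9%. A uniform 10% loss reduces the total to about 102 and leaves the share unchanged. With proportional filling, 0.639 × 68 ≈ 43 places go to low-risk and about 25 to high-risk children. In the top-down arm, 0 of 68 are low-risk.

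**Sensitivity of the share**
- Low-risk remission varied between 48% and 70%, and high-risk MTX remission between 30% and 50%: 53% to 73%.
- High-risk failures entering at twice the low-risk rate: 72.2/(72.2 + 81.6) = 47%. At half the rate: 72.2/(72.2 + 20.4) = 78%.
- All high-risk failures placed first: (68 − 40.8)/68 = 40%.

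**Direction of bias.** Suppose adalimumab remission is 65% in high-risk children (the design rate) and 70% to 90% in low-risk children (my assumption; the article gives no figure). The mix alone then adds 0.639 × (0.70 − 0.65) = 3 points to 0.639 × (0.90 − 0.65) = 16 points to step-up. A penalty for prior failure of the same size cancels it. At 80% in low-risk children, the net shift is +9.6 points with no penalty, about 0 with a 10-point penalty and about −10 with a 20-point penalty.

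**Precision if restricted to high-risk.** Half-width of a 95% interval for the difference, at 65% on both sides: 1.96 × √[0.65 × 0.35 × (1/68 + 1/m)].
- m = 68: 16 points
- m = 41: 18 points
- m = 25: 22 points

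**High-risk arms compared as randomised.** About 68 × 0.9 = 61 are evaluable per arm. If the design rates carry over to month-12 remission, the methotrexate-then-step-up strategy has remission 0.40 + 0.60 × uptake × rescue remission. Rescue remission of 20% to 50% is my assumption.
- Full uptake: 52% to 70%, against 65%. Power is 31%, 12%, 3% and 9% at rescue remission of 20%, 30%, 40% and 50%.
- Uptake of 60% (68/113): 47% to 58%. Power falls from 51% to 12%.

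The difference from 65% detectable with 80% power is about 22 to 25 points.

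**The case against.** The strongest reply is that the limitation is already disclosed. The Discussion says the comparison is not randomised and prone to selection bias, it also gives modest aims (comparison with outside anti-TNF studies and counting who benefits from rescue), and Box 1 labels the top-down side as high-risk. No analysis method for this comparison is described, so stratification or adjustment could sit in the full protocol or SAP. This stands in part. But the two groups are defined in the article itself, the only bias mechanism named is prior failure or intolerance, and the Discussion still looks to the comparison for which patients benefit.

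The 64% is also open to challenge. Month-12 non-remission is not the entry criterion: entry needs failure or inability to stop induction, is optional, and is closed before month 12 in one of the two places that describe it. Methotrexate intolerance is a further route in Box 4, with no rate given. Filling all 68 places needs about 60% uptake. These points stand, which is why a range is given.

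Three stronger readings are tempting and not supported:
- *The comparison favours step-up.* The risk mix pushes that way, but selection on prior failure plausibly pushes the other way.
- *The cap over-represents early failures.* The article does not say how places are filled or that the cap will bind.
- *A randomised version is free.* Comparing the high-risk arms needs no new randomisation. But failures may leave the study, the places are shared with low-risk children, and Treatment discontinuation gives one follow-up visit, either 12 months after starting treatment or on entry to the ancillary study. A month-12 outcome is therefore not clearly assured for every child.

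**Conclusion.** The concern holds as risk-group confounding that the article does not name. About 64% of step-up children would be low-risk against 0% of top-down children. That figure rests on the design remission rates, on month-12 non-remission standing in for failure, and on proportional uptake; other uptake assumptions give roughly 40% to 78%. In none of these scenarios does the imbalance disappear.

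The net direction of bias is unknown, so a reader should not infer that either strategy is favoured. What follows is narrower: the pooled comparison cannot show which children benefit from top-down treatment. This is a secondary, non-randomised comparison, and the primary analysis is unaffected.

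A smaller inconsistency goes with it. The Ancillary study section allows entry until visit 5, while Box 4 offers the switch under a heading that includes visit 6.

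**What to change.** 1. Define the direct comparison as high-risk top-down against high-risk step-up only. Stratifying by risk group comes to the same thing, because no low-risk child receives top-down adalimumab and that stratum contributes no contrast.
2. Report low-risk step-up separately and descriptively.
3. Name the risk-group confounding beside the existing caveat in the Discussion.
4. As a supporting analysis, compare the high-risk arms as randomised on month-12 remission regardless of switch. State that this answers a strategy question rather than how well adalimumab works after failure, that power is limited, and that it needs month-12 outcomes for children who switch or exit. Clarify the follow-up timing under Treatment discontinuation accordingly.
5. Reconcile the last visit for ancillary entry between the Ancillary study section and Box 4.

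The cost is mainly wording, plus securing the month-12 visit for item 4. The price is precision: at most about 41 step-up children on the design rates, or about 25 of 68 if places fill proportionally. The planned 68 v 68 is not reached, and the interval half-width grows from about 16 points to about 18 or 22. Selection by prior failure remains and must still be stated.

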#### Unscheduled visits

Unscheduled visits may be arranged based on clinical requirements. As for scheduled visits per protocol treatment adaptions are possible if intolerance or failure of the study drug is detected. Subsequent scheduled visits will not be changed after an unscheduled visit.

#### Treatment discontinuation

Patients who discontinue treatment before completing 12 months of study drug within either the main study or the ancillary study will receive a single follow-up visit. This will be either 12 months after the commencement of study treatment or at the point of inclusion in the ancillary study.

Modifications to the protocol while the study is being conducted will be relayed to all site staff by email and then onto their relevant ethical and regulatory boards. The current manuscript is based on protocol 5.1 last modified 28 May 2019.

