### Study end points

Patients are followed up for 12 months postrandomisation. The primary end point of the study is sustained steroid or EEN-free remission at 12 months, defined as weighted Paediatric Crohn’s Disease Activity Index (wPCDAI) ≤12.5 and C reactive protein (CRP) ≤1.5 fold upper limit without a relapse or need for EEN/steroids since week 12.

Secondary end points include comparison of time to first relapse, remission at 12 weeks, growth, adverse events, health-related quality of life and patient-reported outcomes between the two treatment arms within each risk group but also between low and high risk MTX treated patients (a full list of secondary endpoints can be found in box 1). The TUMMY CD (patient-related outcome measure) was originally included as a secondary end point but has been withdrawn as the original timetable of development and validation of the score has not been met so it was not ready in time to be included. The study also aimed to evaluate clinical predictors for response, including genomic and serological markers and results of drug monitoring (MTX and ADA concentrations) metabolites (6-thioguanine (6-TG) and 6-methylmercaptopurine (6-MMP) in AZA/6MP) and antidrug antibodies (ADA) in relation to adherence, toxicity and response. The ancillary study additionally aimed to evaluate the efficacy of ADA in patients treated from inclusion (top-down) versus patients switched to ADA due to immunomodulator failure (step-up). Further outcome measures are detailed in box 1.

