### Follow up visits (visit 2, 3, 4, 5 and 6)

Patients are followed up at prespecified intervals (figure 1) with a window of ±2 weeks. A telephone call is undertaken at week 4 following initiation of induction in order to support patient compliance with induction regime and advise weaning where appropriate. Data as described in box 3 are collected at each consultation. Patients’ compliance with therapy is determined at each face-to-face follow-up visit by pill and vial counts plus by patients’ reporting.

Box 3Standard requirements for each study visitAn explicit history of illness since last visit, including review of symptoms, medications (including compliance check) and adverse events.Physical examination weighted Paediatric Crohn’s Disease Activity Index (wPCDAI), physician global assessment and PCDAI scoring.Anthropometrics (height measured using a calibrated wall mounted stadiometer).Blood tests.White blood cells.Absolute neutrophil count.Haemoglobin.Haematocrit.Platelet count.Erythrocyte sedimentation rate.C reactive protein.Amylase.Albumin.Aspartate transaminase.Alanine transaminase.Conjugated bilirubin.Gamma glutamyl transferase.Stool samples for faecal calprotectin and microbiome analysis.Health economic parameters (EQ-5D-Y proxy 1; EQ-5D-Y; EQ-5D-5L; WPAI:Crohn’s disease; school attendance questionnaire).Quality of life evaluation (IMPACT 3).Urine human chorionic gonadotropin in all female patients of childbearing potential.Confirmation of contraception use or of absolute abstinence in all patients.

Remission is defined as wPCDAI≤12.5, normal CRP (≤1.5 times upper normal range) and being free of steroids or EEN. Once remission is achieved and induction therapy is discontinued, a patient is considered to be failing treatment or experiencing a relapse in the following circumstances:

wPCDAI >40.CRP >2 times upper normal limit in the absence of any clear infectious process.wPCDAI >12.5 but <40 and/or CRP >1.5 times but <2 times over upper normal limit at two consecutive visits within 2–8 weeks.Development of CD-related complications, for example, fistulisation.Requirement for additional CD-specific medication/surgery since last study visit.

A patient will also be considered a treatment failure should induction therapy be continued at week 12. In addition, the treating clinician may escalate treatment at any time point independent of wPCDAI score if it is felt that the patient is experiencing a relapse.

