#### Dose optimisation and therapeutic drug monitoring

Drug monitoring is undertaken as detailed below. In addition to this, samples for drug monitoring should be collected at the time of medication cessation in the event of drug discontinuance due to adverse effect or loss of response. Potential adaptations to therapies which may be made at specific follow-up visits are detailed in box 4.

Box 4Potential adaptations to therapies at follow-up visitsMonth 2 (visit 2)Failure to discontinue induction therapy by week 12Offer switch to the ancillary study (adalimumab (ADA) step-up) to those prescribed methotrexate (MTX) or azathioprine (AZA)/6-mercaptopurine (6MP), or an increase in dose frequency to weekly in those prescribed ADA.Alternatively, the patient may leave the study and receive therapies as per the discretion of the treating clinician.Months 4, 6, 9 and 12 (visits 3, 4, 5 and 6)Thiopurine non-response.Protocol as per metabolite levels (detailed in table 3).Thiopurine intolerance (except pancreatitis).Switch to alternate thiopurine (AZA to 6MP or vice versa) or split dose to provide twice daily (BD) dosing.Thiopurine failure (any exacerbation despite dose optimisation/pancreatitis/cytopaenia).Offer switch to ancillary study (ADA STEP-up) or exit study.MTX intolerance or failure (any exacerbation or elevation of liver enzymes as detailed below).Offer switch to ancillary study (ADA STEP-up) or exit study.ADA failure (any exacerbation).Increase frequency to weekly dosing.

**Table 3 T3:** Azathioprine dose adjustments based on metabolite levels

Result	Action
6-TG <150	Consider non-compliance; repeat sample at subsequent visit and increase dose if low 6-TG confirmed (+25 mg or +12.5 mg if dose <50 mg).
6-TG 150–800	No adaptation.
6-TG >800	Decrease dose if repeat sample at subsequent visit confirms high 6-TG (−25 mg or −12.5 mg if dose <50 mg).
6-MMP >8000 or signs of hepatotoxicity	Stop medication—switch to ancillary study. Erythrocyte lysate sample frozen at −80°C and shipped to central lab at end of study for thiopurine nucleotides.

6-MMP, 6-methylmercaptopurine.

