### Allocation concealment and blinding

For ethical reasons, we decided against a double dummy design for blinding the patient, parents and care givers. Due to the differences in medication administration route and the significant nausea commonly associated with MTX blinding of the allocation to the patients, their families or their physicians is not possible. Where possible, however, blinding of an alternative clinician to score the wPCDAI, PCDAI and physician global assessment at each study visit should occur (prospective randomised open blind end-point (PROBE) evaluation).

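### Stopping study drug cuts follow-up to one visit, so relapse between week 12 and month 12 is incompletely observed in children who stop without a recorded failure

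*Protocol article*

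**What the plan says.** **Endpoint.** The Study end points section defines success as wPCDAI and CRP within limits at month 12 "without a relapse or need for EEN/steroids since week 12". Box 1 adds time to first relapse after week 12, which the Secondary analyses section assigns to Kaplan-Meier, log-rank and Cox methods. The same Study end points section states: "Patients are followed up for 12 months postrandomisation".

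**Relapse.** The Follow up visits section defines relapse by a high wPCDAI, a high CRP, lesser elevations "at two consecutive visits within 2–8 weeks", a Crohn's complication, or new Crohn's medication or surgery since the previous visit. Box 3 requires a history of illness and medication since the last visit at every study visit.

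**After stopping.** The Treatment discontinuation section covers "Patients who discontinue treatment before completing 12 months of study drug". They "will receive a single follow-up visit", and on timing: "This will be either 12 months after the commencement of study treatment or at the point of inclusion in the ancillary study".

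**Routes off drug (Box 4).** For MTX intolerance or failure, and for thiopurine failure, the action is: "Offer switch to ancillary study (ADA STEP-up) or exit study". Thiopurine intolerance other than pancreatitis leads to a change within the class or a split dose. For adalimumab failure Box 4 lists only a change in dosing frequency. Box 5 also recognises stopping for intolerance, at the participant's request, or on the physician's judgement.

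**The concern.** The endpoint is a statement about an interval of about nine months, but after stopping drug a child is examined only at the end of it. The wPCDAI and CRP limbs of the relapse definition need measurements made during the interval. Visits 3 to 5 supply most of them, and those visits lapse once drug is stopped.

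Two outcomes are affected. A child who relapses after stopping and is back within limits at month 12 may be counted as in sustained remission. A relapse first seen at month 12 enters the time-to-relapse analysis at the wrong date.

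The effect need not be equal across arms. MTX is one arm of both randomised comparisons. The Allocation concealment and blinding section itself refers to "the significant nausea commonly associated with MTX", and an MTX-intolerant child who declines adalimumab leaves the visit schedule, whereas most thiopurine-intolerant children stay on study drug and on all visits. Completeness of the primary outcome could therefore depend on treatment.

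**Working it through.** **1. Who is affected.** Children who stop because of failure already have their event recorded, and those who enter the step-up study continue to be seen there. What remains is children who stop for intolerance, by request or on the physician's judgement and do not start adalimumab. The Ancillary study section limits step-up entry to 68 patients and to the period before visit 5 ends it, so some children may have no step-up option.

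**2. The plan's own figures.** The Sample size considerations section gives 48% v 70% (low risk) and 40% v 65% (high risk), two-sided 5%, power 80%, loss 10%. The pooled-variance formula is
n = [1.96 √(2p̄(1−p̄)) + 0.842 √(p₁(1−p₁)+p₂(1−p₂))]² / (p₁−p₂)².
- Low risk: n = 78; 78/0.9 = 86.7, so 87 per arm (plan: 88).
- High risk: n = 62; 62/0.9 = 68.9, so 69 per arm (plan: 68).

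Both reproduce to within one child. The 10% allowance is 0.10 × 88 = 8.8 and 0.10 × 68 = 6.8 children per arm. It concerns loss to follow-up. No rate of stopping drug is given.

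**3. Overstatement within one arm.** Let d be the share of the arm in the affected group, r the share of those who relapse before month 12, and u the share of those relapses that leave no record and have resolved by month 12. Overstatement = d × r × u. All three are assumptions: d 10–20%, r 30–50%, u 30–50%.
- Low end: 0.10 × 0.3 × 0.3 = 0.009, about 1 point.
- High end: 0.20 × 0.5 × 0.5 = 0.05, or 5 points.
- If history captures everything, u = 0 and the overstatement is 0.

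**4. Difference between arms.** Write h = r × u. With equal true rates, the spurious difference is (d₂ − d₁) × h in favour of the arm with more stops. Type I error uses a normal approximation, with 48% and 88 per arm (low risk) or 40% and 68 per arm (high risk).

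| d₁ v d₂ | h | Difference (points) | Type I error, low risk | Type I error, high risk |
|---|---|---|---|---|
| 5% v 15% | 0 | 0 | 5.0% | 5.0% |
| 5% v 15% | 0.25 | 2.5 | 6.3% | 6.0% |
| 5% v 15% | 0.50 | 5.0 | 10.2% | 9.0% |
| 5% v 25% | 0.25 | 5.0 | 10.2% | 9.1% |

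The assumptions in step 3 give h of at most 0.5 × 0.5 = 0.25, so the third row is already beyond them.

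**5. Dependence on scoring.** If every affected child were instead scored as not in remission, and the true rate is the same in stoppers and others, each arm's rate becomes p(1 − d). At 5% v 15%:
- Low risk: 0.48 × 0.85 − 0.48 × 0.95 = 0.408 − 0.456 = −4.8 points.
- High risk: 0.40 × 0.85 − 0.40 × 0.95 = 0.340 − 0.380 = −4.0 points.

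The sign reverses and now counts against the arm with more stops.

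**6. The two-visit limb.** Box 4 places visits 3 to 6 at months 4, 6, 9 and 12. A three-month gap is about 13 weeks, and at least 9 weeks even if both ±2-week windows are used. Visits 4–5 and 5–6 therefore cannot satisfy a 2-to-8-week interval for any child, on drug or off.

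**The case against.** Several stronger readings are tempting, and the documents do not support them.

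- **That relapse cannot be observed at all after stopping.** The month-12 visit takes a history since the last visit. New Crohn's medication, surgery and complications count as relapse, and steroid or EEN need is part of the endpoint. What can escape is a wPCDAI- or CRP-defined relapse that led to none of these and has resolved by month 12.
- **That the arm with more drop-outs will show fewer relapses.** The shift is zero when history is complete, and it reverses if stoppers are scored as non-remission. A child who stops and starts another Crohn's drug could also be scored as a relapse, which again counts against the arm with more stops.
- **That leaving the study under Box 4 means no visit at all.** This is one reading. The Treatment discontinuation section promises a visit to those who stop drug and makes no exception for these children.
- **That the single visit disables the two-visit limb.** By step 6, scheduled visits fail that limb for everyone over the last six months, and it relies on unscheduled visits.
- **That thiopurine patients always stay on the schedule.** Pancreatitis and cytopaenia count as thiopurine failure with the same switch-or-exit route, and Table 3 stops drug for high 6-MMP or hepatotoxicity. The asymmetry is real for most intolerance, but not complete.

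It is also fair to say that the scoring of discontinuers belongs to an analysis plan that is not shown, and that every input in step 3 is assumed. These objections narrow the point but do not remove it: an analysis plan cannot supply wPCDAI and CRP values that the visit schedule never collected, and history cannot date an untreated flare reliably.

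**Conclusion.** The point holds in a limited form. The follow-up rule after stopping drug does not fit a primary endpoint and a time-to-relapse outcome defined over week 12 to month 12. For children who stop without a recorded failure and do not start step-up adalimumab, some relapses can be missed and others dated late. Because routes off drug differ by arm, ascertainment may differ as well.

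Neither the direction nor the size can be determined from the documents. The illustrative range is 0 to about 5 points, against design differences of 22 and 25 points. It rests on assumed stopping rates and assumed proportions of unseen, resolved relapses. This does not change the sample size. The main reason to act is that the improvement is cheap and that the missing measurements cannot be recovered later.

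**What to change.** Amend the Treatment discontinuation section, and reconcile it with Box 4 and the 12-month follow-up statement in Study end points, so that stopping study drug does not stop assessment. Every randomised child keeps scheduled visits 3 to 6 on the original dates unless consent is withdrawn, whatever treatment is then taken, and relapse is assessed at each. Say explicitly that leaving study treatment under Box 4 is not leaving follow-up.

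This restores the single-visit wPCDAI and CRP criteria and the dating of relapse. It does not restore the two-visit criterion over the last six months, which the visit spacing prevents for all children. No scoring rule for discontinuers is proposed here: it is a trade-off, as step 5 of the working shows, and belongs in the analysis plan.

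The cost is protocol wording and continued contact with children who are off study drug, at visits already planned for everyone.
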